While these individuals with personality difficulties do still benefit from TTad interventions, their rates of clinically significant improvement and recovery are lower than in those individuals without personality difficulties. For example, recovery rates for this group are estimated to be around 40%, below the 50% national target, and the 50.2% observed recovery rate observed across all client groups in 2020–2021 [1, 10]. These effects held over and above intake depression and anxiety severity, other demographic features, and number of treatment sessions attended [4, 5].

A subtly different pattern emerges in reviews of CBT outcomes in the clinical trials literature [11, 12]. While there is evidence that clients with a comorbid personality disorder diagnosis have higher symptom levels at the end of CBT treatments for both anxiety and depression, this effect does not consistently emerge when controlling for intake depression and anxiety symptom severity [11, 12]. These secondary analyses are at risk of type II error as the studies were not powered for subgroup analyses and did not stratify clients to treatment on the basis of personality disorder subgroup status. Nevertheless, current data suggest that therapists delivering CBT under ideal conditions can achieve broadly comparable levels of change in clients with and without a comorbid diagnosis of personality disorder. This suggests therapists in TTad settings may benefit from additional training to optimise their ability to deliver existing CBT treatments in the context of these more complex presentations, rather than there being a need to introduce entirely new treatment protocols.

In qualitative evaluations, TTad clients with personality difficulties describe how care has not always felt tailored to their needs [13] and TTad clinicians report feeling unskilled and lacking in confidence to undertake therapy with this client group, and propose core TTad training should include focused training on this topic [14]. In particular, clients viewed more structured approaches as less acceptable and valued more flexible approaches [13], and therapists were less likely to report difficulties ‘maintaining control’ over sessions if they adopted more flexible approaches [14]. Furthermore, recent updates to clinical guidance on depression now reflect the importance of assessment of interpersonal difficulties and tailoring care to cover these issues where they are acting to maintain depression [15].

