### The intervention

The 1-day workshop has three main themes: (1) psychoeducation about personality difficulties; (2) building skills, knowledge, and motivation to better meet the needs of clients with personality difficulties when delivering a CBT protocol for anxiety or depression; and (3) highlighting the importance of, and considering how to build, therapist self-care and resilience when working with more complex clients. The content of the workshop is informed by the CBT evidence base, including guidance about how to adapt CBT for complex cases [24, 25] and for personality disorders [26, 27]. The intention is to make ‘explicit’ what is often ‘implicit’ good practice in how TTad therapists are supporting this client group in a way that supports fidelity to the CBT treatment protocol rather than leading to unhelpful therapist drift.

The training is delivered by two experienced CBT trainers (online or face-to-face) and is a combination of didactic teaching, small group exercises, role play illustration, and role play practice of the techniques; in line with the declarative-procedural-reflective (DPR) model of therapist knowledge acquisition and the COM-B model of behaviour change [28, 29]. A detailed logic model of change underpinning the training (developed retrospectively) is included in Additional file 1: Appendix 1.

The objectives of theme 1 are to build therapist knowledge and understanding about the dimensional framework for personality disorders proposed in ICD-11 [7, 8, 30]; to better understand how these features relate to therapy outcomes; to reduce stigma and ambivalence to working with these clients; and to build skills to assess current severity accordingly of these features to inform if a client is likely to benefit from therapy in a TTad service. Updates to clinical guidance are also covered, highlighting that individuals with comorbid formal personality disorder diagnoses should not routinely be denied access to treatments for depression/anxiety [15], although those with more severe presentations may be more appropriately managed in secondary care services like community mental health teams or specialist personality disorder teams rather than in primary care TTad settings.

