	Percentage of attending therapists completing 3-month follow-up surveys	≥ 60% data availability
**Acceptability**	*Quantitative data*	
	Feedback data on training (that that the training was theoretically interesting, clinically useful, well presented, and would recommend to other HICBT therapists)	60% agree or strongly agree with each item
	*Qualitative data*	
	Written feedback from therapists on the value of training	No significant concerns emerge about training that cannot be resolved
	Qualitative interviews with therapists	No significant concerns emerge about training that cannot be resolved
	Reporting/identification of serious concerns about the acceptability and feasibility of training by key stakeholders	No serious concerns emerge about training that cannot be resolved
	Reporting/identification of serious negative consequences for therapist participants or the clients they subsequently work with as a result of the training (unexpected, clearly research- or training intervention-related serious adverse reactions).	No serious consequences raised
**Clinical outcome data completion**	*Quantitative data*	
	Percentage of TTad clients receiving routine care during the study with sufficient data for inclusion in secondary analyses (at least one measure of SAPAS-SR personality difficulties and at least × 2 measures of the TTad service minimum dataset [PHQ-9, GAD-7 and WSAS])	≥ 60% data availability
**Proof-of-concept**	*Quantitative data*	
	Therapist attitudinal change in confidence to recognise, assess and triage clients with personality difficulties; to adapt key skills for working therapeutically with this group; and in positivity towards working with this group after completing the training in each service.	Significant improvement from pre to post in all 5 attitudinal domains

In addition to these measures, we will capture clinical data to enable us to generate metrics of engagement including discharge code and number of sessions marked ‘Attended’, ‘Did Not Attend’, and ‘Patient Cancelled’. In line with standard reporting of TTad outcomes, we will also compute the following metrics from clinical outcomes: (i) ‘Recovery’—as defined by moving ≥ 10 to ≤ 9 on the PHQ-9 and from ≥ 8 to ≤ 7 on the GAD-7; (ii) ‘Reliable Improvement’—as defined by improving by ≥ 6 points on the PHQ-9 or ≥ 4 points on the GAD-7; and (iii) ‘Reliable Recovery’—as defined by fulfilling criteria for both ‘recovery’ and ‘reliable improvement’ [49].

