#### Service-level secondary data sample

No clients will be recruited for the study. We will perform exploratory secondary analyses on routinely collected and anonymised clinical outcomes data and Patient Experience Questionnaires, focusing on those with personality difficulties. This will be defined as scoring 3 or more on the Standardised Assessment of Personality: Abbreviated Scale—Self Report version (SAPAS-SR) [47, 48]. Considering TTad caseloads and estimates of personality disorders in this setting, we estimate that 40 therapists in each site (120 in total) will treat > 20 clients each in a 6-month period before and the 6-month period after the training, creating an estimated sample size of > 4800 service-users (~ 2400 before and ~ 2400 after). Based on previous studies examining the prevalence of personality difficulties in TTad services, we anticipate between 69 and 81% will meet the criteria for probable personality disorder [5, 9] in both pre- and post-training cohorts. The purpose of this secondary analysis will be to determine preliminary proof of concept that the training has the potential to improve service level outcomes for this population and to inform the power calculation for a subsequent randomised definitive evaluation.

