#### Clinical outcomes

We will report descriptive statistics (means, standard deviations) to describe the clinical measures and client characteristics at intake within the pre- and post-training intervention cohorts (those engaging in treatment in the 6 months pre- compared to 6 months post-therapist training). This will include PHQ-9, GAD-7, and WSAS mean scores; the proportion of clients showing mild, moderate, and severe cut-offs on each scale; and the proportion of clients scoring 3 or more on the SAPAS-SR (indicative of personality difficulties).

This research is a multi-site observational study prior to conducting a definitive evaluation with a randomised trial and therefore has not been a priori powered to inferentially examine between cohort differences in clinical outcomes. However, it is both possible and useful to estimate the between-cohort effect size (and their 95% confidence interval) on client outcomes to help inform decisions to continue to a definitive evaluation of the training intervention and to inform future power calculations. We will therefore report the observed effect sizes but not *p* values. These analyses will focus solely on the subgroup of participants meeting the criteria for probable personality disorder (3 or more on the SAPAS-SR), which we estimate from previous research to be between 69 and 81% of client treatments [5, 9]. A series of linear regressions will examine whether treatment-cohort (treated before or after training) predicts the number of treatment sessions attended and post-treatment levels of depression (PHQ-9), anxiety (GAD-7), and functioning (WSAS). All analyses will include the training site as a covariate. The post-treatment analyses will adjust for the pre-treatment level of the relevant variable. Comparable binary logistic regressions will examine binary outcomes (rates of reliable improvement, recovery, and reliable recovery; rates of clients with planned discharges), again seeing if the treatment cohort (before or after training) predicts each variable and covarying for the training site. As we do not anticipate sufficient statistical power to do inferential statistics, we will examine the distribution of effect sizes, potentially using confidence intervals and Bayesian methods relative to estimates of minimum clinically important difference on clinical outcomes (cf., [55–58]). All quantitative analyses will take place in SPSS or R.

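### The logistic models for recovery, reliable improvement and reliable recovery name only cohort and site, although these outcomes are built from intake PHQ-9 and GAD-7 scores and the cohorts are not randomised

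*Protocol article*

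**What the plan says.** The Clinical outcomes section under Statistical methods compares clients treated in the 6 months before the workshop with those treated in the 6 months after, among clients scoring 3 or more on the SAPAS-SR. Site is a covariate in every analysis. For the linear models of final PHQ-9, GAD-7 and WSAS it adds: "The post-treatment analyses will adjust for the pre-treatment level of the relevant variable".

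The logistic models come next: "Comparable binary logistic regressions will examine binary outcomes", namely the three symptom-based rates and planned discharge, "again seeing if the treatment cohort (before or after training) predicts each variable and covarying for the training site". No intake score is named there, and SAPAS-SR score is a covariate in no model.

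The Outcomes section (text after Table 2) defines recovery "as defined by moving ≥ 10 to ≤ 9 on the PHQ-9 and from ≥ 8 to ≤ 7 on the GAD-7" and reliable improvement "as defined by improving by ≥ 6 points on the PHQ-9 or ≥ 4 points on the GAD-7". Reliable recovery requires both.

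The Clinical outcomes section reports effect sizes with 95% confidence intervals and no p values. Their stated use is to inform the decision to continue to a definitive evaluation and future power calculations. Intake scores and severity bands will be tabulated by cohort.

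**The concern.** The plan controls for starting severity when it analyses the scores, but does not say that it does so when it analyses rates derived from the same scores. Each of the three rates depends on where the client starts. Nothing in a before/after design makes the two cohorts start at the same level: referral patterns can drift, and case mix could change after training.

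An odds ratio adjusted only for site would then combine case-mix change with any training effect. It could suggest a benefit or a harm where there is neither, in figures intended for the progression decision and for sizing the later trial.

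**Working it through.** **1. The plan's own sample figure.** 120 therapists × 20 clients = 2,400 per cohort, and × 2 = 4,800. This reproduces the figure in the Service-level secondary data sample section. With 69% to 81% scoring 3 or more on the SAPAS-SR, the analysed subgroup is 0.69 × 2,400 = 1,656 to 0.81 × 2,400 = 1,944 per cohort.

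**2. Precision of a recovery difference.** The Background gives the rate: "recovery rates for this group are estimated to be around 40%, below the 50% national target". The 95% half-width is 1.96 × √(2 × 0.4 × 0.6 / n).

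- n = 1,656: 3.3 percentage points. n = 1,944: 3.1 points.
- If only 60% have usable data (the Table 2 threshold), n = 994 to 1,166 and the half-width is 4.3 to 4.0 points.

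**3. Why intake matters.** Suppose the final score is a constant + b × intake + noise, with b between 0 and 1. A higher intake score raises the expected final score, so fewer clients end below threshold. The expected drop is (1 − b) × intake − constant, so a higher intake score also makes a drop of 6 or 4 points more likely. Among clients who are cases at intake, recovery and reliable improvement therefore respond in opposite directions.

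**4. Simulation with no training effect.** The article gives no intake means or SDs, so these inputs are assumptions:

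- intake PHQ-9 mean 16 (SD 5.5), GAD-7 mean 14 (SD 4.5), correlation 0.6;
- b = 0.3, 0.5 or 0.7; residual SDs 5.0 and 4.3;
- before-cohort recovery calibrated to 40% among cases (PHQ-9 of 10 or more, or GAD-7 of 8 or more);
- site held constant.

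The after cohort starts 1 PHQ-9 point lower, with GAD-7 lowered in proportion to its SD. Each cell shows the before and after rates, then the cohort odds ratio (OR) without intake scores.

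| b | Recovery among cases | Reliable improvement, all clients | Reliable recovery among cases |
|---|---|---|---|
| 0.3 | 40.1% to 41.9%, OR 1.077 | 79.5% to 76.1%, OR 0.822 | 38.9% to 40.2%, OR 1.058 |
| 0.5 | 40.0% to 42.8%, OR 1.125 | 81.2% to 78.5%, OR 0.842 | 38.8% to 41.2%, OR 1.106 |
| 0.7 | 40.1% to 43.8%, OR 1.164 | 82.8% to 81.0%, OR 0.887 | 39.0% to 42.4%, OR 1.149 |

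Check for b = 0.5, recovery: (0.428/0.572) / (0.400/0.600) = 1.12 from the rounded rates.

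Other shifts among cases:

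- 0.5 points lower: recovery OR 1.04 to 1.09, reliable improvement OR 0.90 to 0.95.
- 2 points lower: recovery OR 1.15 to 1.34, reliable improvement OR 0.67 to 0.79.
- 1 point higher: recovery OR roughly 0.85 to 0.92, reliable improvement OR roughly 1.1 to 1.25.

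**5. With intake PHQ-9 and GAD-7 added.** The cohort odds ratio returns to 0.99 to 1.01 for all three outcomes in every scenario. The true value is 1.00.

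**6. Sensitivity to the recovery denominator.** Read literally, the definition requires both intake scores to be above threshold. If that definition is applied to every client in the subgroup, a lower intake makes fewer clients eligible while making those who are eligible more likely to recover. The two effects largely cancel. The unadjusted recovery odds ratio is then about 0.93 to 1.04 for a 1-point shift in either direction, with no consistent sign. Reliable improvement has no such denominator and stays biased.

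**7. Bias against precision.** Among cases, a 1-point lower intake moves recovery by 1.8 to 3.7 points and a 2-point lower intake by 3.4 to 7.2 points. The half-width is 3.1 to 3.3 points, or somewhat more if only cases are counted.

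**The case against.** **The wording may already cover it.** "Comparable binary logistic regressions will examine binary outcomes" follows directly on the sentence about baseline adjustment, so that adjustment may be meant to carry over. This reading is possible but does not settle the matter. The logistic sentence goes on to name site, which was already required everywhere, and leaves the intake score out. A composite of two scales also has no single relevant variable, so an analyst would still not know what to enter.

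**A shift by design is not supported.** A reader might infer that the training is meant to change intake severity, because the workshop aims to "build skills to assess current severity accordingly of these features to inform if a client is likely to benefit from therapy". The article does not support this. That sentence concerns personality features, not depression or anxiety scores. The same section says that more severe presentations may belong in secondary care, but also that people with a formal diagnosis should not be routinely refused treatment, so the content pulls both ways. The Discussion adds that low-intensity staff, who are not trained here, often carry out the intake assessments. A case-mix change is plausible but is not a stated aim.

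**Opposite-direction bias is not general.** A reader might also infer that recovery and reliable improvement are always biased in opposite directions. That holds only when recovery is computed among cases, a denominator the article does not state.

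**The consequences are limited.** There are no p values. Intake scores are tabulated by cohort, so drift would be visible, and the score models shown alongside are baseline-adjusted. Table 2 sets no continuation rule on client outcomes, only on the completeness of their data. All of this stands and limits the severity. However, a table of intake scores shows a confounder without removing it, and the estimates are still intended to inform continuation and the later power calculation.

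**Conclusion.** The concern holds in a limited form. The article names baseline adjustment for the score models and only cohort and site for the logistic models, although the three symptom-based rates are functions of intake and final scores. Any intake difference between cohorts, from secular drift or changed case mix, would then be read as a training effect.

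For a 1-point shift, the false odds ratio for reliable improvement is about 0.8 to 0.9 or 1.1 to 1.25, depending on direction. For recovery among cases it is about 0.85 to 0.92 or 1.08 to 1.16, a bias similar in size to the confidence half-width. Over all clients the recovery bias is small and of uncertain sign. These figures rest on assumed score distributions and an assumed shift. The article gives neither, and with no shift there is no bias. The point is worth correcting because the remedy uses data already in hand, but it does not undermine the feasibility aims.

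**What to change.** In the Clinical outcomes section, state that the logistic models for recovery, reliable improvement and reliable recovery include intake PHQ-9 and intake GAD-7, both scales in each model, alongside cohort and site.

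Add SAPAS-SR total as a further covariate in these three models. Restricting to scores of 3 or more does not equalise severity above that cut-off, and symptom scores alone would not remove a shift in personality severity. The Background reports that personality difficulties predict poorer outcome even after allowing for intake symptoms.

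The cost is small: one sentence of text, slightly more modelling, and possibly a few cases lost to a missing covariate. The loss should be slight, because the data-sufficiency criterion in Table 2 already requires a SAPAS-SR measure and at least two measures of the minimum dataset. Adding WSAS to every model and reporting marginal risk differences are optional.

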#### Qualitative analysis

Written qualitative feedback will be anonymised and interviews transcribed verbatim and anonymised prior to any analysis. Both datasets will be explored using a framework method to support the systematic refinement of themes to understand experiences and their meanings [30, 51]. Analysis of therapist qualitative data will be both inductive and deductive, informed by behavioural change theory (COM-B [29] and Normalisation Process Theory [50]) in order to explore barriers and enablers to implementation of the skills practiced during the training, as well as the implementation of this training workshop more broadly into routine HICBT therapist training. The analysis will be an iterative process involving close reading and familiarisation with the data, coding, comparison, and refinement and elaboration of emerging themes. NVivo will be used to support qualitative data management.

Findings will indicate therapists’ views on the feasibility and acceptability of the training and the research procedures involved. They will inform future refinement of the training intervention, as well as whether trial procedures need amendment before continuation to a definitive trial.

## Discussion

Individuals with comorbid personality difficulties make up a significant proportion of the TTad population and have a poorer response to depression and anxiety treatments compared with those without these additional difficulties [4, 5, 9]. TTad clinicians also report feeling unskilled to undertake this work, despite recognising that working with this population is central to their care context [13, 14]. Therefore, delivering additional training to TTad clinicians represents a significant opportunity to improve therapist knowledge, skill, and confidence and to improve care and outcomes for clients.

Other research has reported that training interventions for healthcare staff to improve understanding of personality disorders has led to shifts in workforce attitudes towards individuals with personality disorders and reductions in staff burnout (e.g. [18, 19]). However, interventions tailored to a HICBT workforce aiming to enhance skills specific to their type of clinical work have not previously been formally evaluated. This study will therefore, for the first time, evaluate a HICBT therapist-specific training workshop across multiple TTad services to improve understanding and tailoring of care for individuals with secondary personality difficulties. However, the current training focuses solely on high-intensity therapists, which is only a subset of the TTad workforce. In due course, we think there is a need to develop and evaluate comparable training for the low-intensity (Psychological Wellbeing Practitioner) therapists, who deliver a large proportion of care and often conduct initial intake assessments in a majority of TTad services.

Through an embedded secondary analysis of routine clinical outcomes, this study will also establish whether training shows the potential to lead to improvements in clinical outcomes for individuals receiving TTad treatments who present with secondary personality difficulties.

Together these findings will inform the future investigation of this approach and whether to proceed to a definitive randomised controlled trial powered to test the clinical effectiveness and cost-effectiveness of the training intervention.

